**“NODIVEM” study. (Ethical Committee approval : CPP NO 2011/030, October 21th 2011)**

With the increasing use of chest CT scan in high risk subjects and its ability to detect early stage peripheral lung cancer, solitary pulmonary nodule diagnosis has become a major challenge in respiratory clinical practice. Their management is difficult and, according to published guidelines, often requires close CT follow up, PET CT and invasive procedures to obtain a definite histology. In this context, innovative endoscopic techniques such as electromagnetic navigation and endoscopic ultrasound using radial miniproboscopes (EBUS) - also referred as navigational bronchoscopy – have proved to be efficient, in the localization and sampling of peripheral lung nodules that are superior to 20 mm in size. However, none of these techniques is able to differentiate malignant lesions from benign ones, in-vivo, in real time. We have recently developed the technique of confocal endomicroscopy of the distal lung –also referred as distal lung pCLE or “Alveoscopy” - and published the first images of confocal endoscopy of the normal and tumoral distal lung acquired in vivo.

In this prospective trial we will assess confocal endoscopy as a tool to localize the peripheral lung nodules and to differentiate benign from tumoral lesions.

**Objective(s) of the clinical study**

1. To demonstrate that confocal endomicroscopy is not inferior to navigational endoscopy for the localisation of peripheral lung nodule
2. To demonstrate that confocal endoscopy can differentiate benign from malignant tumors

**Main assessment criteria:**

1. number of lesions localized by confocal endoscopy compared to navigational bronchoscopy
2. Positive and negative predictive values of confocal signs before and after IV fluorophore injection for the diagnosis of cancer.

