**Statistical evaluation :**

In this study, positive diagnostic criteria for the localization of peripheral nodule using confocal imaging is a solid pattern as opposed to the usual loose fibered network pattern of the normal alveolar duct. According to this criteria, the confocal imaging procedure will be considered as valid if the number of lesions recognized by confocal is not inferior to 90 % of those localized by navigational bronchoscopy. Therefore, pCLE will prove valid if it can recognize at least 71 of 78 nodules / subjects efficiently sampled using navigational bronchoscopy (Cohen concordance Kappa value of 0,74 between confocal and navigational bronchoscopy).

A secondary objective will be to describe specific signs of cancer using confocal endoscopy . This will be assessed on the first 30 patients (including 20 cancers) using confocal imaging obtained before and after fluorophore IV injection, in comparison to histology, and confirmed on the following 48 patients.

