#### *II.1.3. Alveoscopy sequences analysis*

Final detailed analysis of alveoscopy sequences will be performed at the Rouen University Hospital, by an independant observer, blindly from the histology results. For this purpose, several items will be analyzed and

coded such as general organisation of the elastin network, solid pattern, vascular network organisation after fluorescein IV injection, or any other items that would appear significant to differentiate benign from malignant lesions.

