#### **III.2. Objectives**

##### *III.2.1. Primary objective*

To determine if Alveoscopy can help to the localization and sampling of a peripheral lung nodule in vivo in showing a solid pattern.

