##### *III.2.2. Secondary objectives*

- a. To determine Sensitivity, specificity, positive and negative predictive values of alveoscopy signs for the differentiation between benign and malignant nodules.
- b. To confirm the good tolerance of the technique

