### *III.3.3. Secondary criteria analysis :*

Positive predictive value of confocal imaging for the differentiation of benign versus malignant lesion will be calculated based on histology of the lesion and pertinent in vivo imaging items that will be describe during the study. This semiology will be described from the first 30 patients (including 20 malignant lesions) among the 78 patients for which a definite diagnosis is obtained by the procedure.

The value of this semiology will be confirmed on the 48 further patients.

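### Benign/malignant differentiation is listed as a main criterion to be demonstrated but planned as a secondary objective, and its confirmation in 48 patients has no reference value

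*Protocol*

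**What the plan says.** The two lists headed Objective(s) of the clinical study and Main assessment criteria appear in the opening summary and again in the synopsis. Both times the second objective reads "To demonstrate that confocal endoscopy can differentiate benign from malignant tumors" and the second main criterion reads "Positive and negative predictive values of confocal signs before and after IV fluorophore injection for the diagnosis of cancer".

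Other sections rank the same work lower. The opening Experimental plan and the synopsis's Statistical evaluation say "A secondary objective will be to describe specific signs of cancer using confocal endoscopy". Section III.2.1 gives one primary objective, on localisation: "To determine if Alveoscopy can help to the localization and sampling of a peripheral lung nodule in vivo in showing a solid pattern". Section III.2.2 lists under secondary objectives "To determine Sensitivity, specificity, positive and negative predictive values of alveoscopy signs for the differentiation between benign and malignant nodules". Section III.3.3 analyses differentiation as a secondary criterion and mentions PPV only.

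On the signs, section II.1.3 names a few items to be coded and then adds "or any other items that would appear significant to differentiate benign from malignant lesions". Section III.3.3 states "This semiology will be described from the first 30 patients (including 20 malignant lesions) among the 78 patients", and then "The value of this semiology will be confirmed on the 48 further patients". Section IV.6 puts the development step at 38 informative cases instead of 30. It adds that the later patients are read by an independent observer blind to histology.

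The 5% alpha, 80% power and 78 navigation-positive patients in section III.3.2 all belong to localisation.

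**The concern.** Two things are at stake. The first is what the trial may claim. A reader of the summary lists would expect a main, demonstrated result on benign versus malignant. A reader of sections III.2 and III.3 would expect a secondary result from a trial sized for something else. The Protocol must settle this itself, because it contains both statements.

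The second is what confirmation means. A PPV has to be read against the cancer prevalence in the same patients. Where two thirds of the nodules are malignant, a sign that carries no information will still look right about two times in three. With an open list of signs, two imaging states and no reference value, a sign could be reported as confirmed without being associated with cancer at all.

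**Working it through.** **The plan's own figures.** 78 / 0.65 = 120, and 30 + 48 = 78; both reproduce. With the 38 of section IV.6, only 78 − 38 = 40 of the 78 would remain for confirmation, not 48. No figure for alpha, power or sample size is given for the predictive values, so there is none to reproduce.

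**Expected PPV of a useless sign.** If a sign is equally frequent in malignant and benign nodules, its expected PPV is about the prevalence: 20/30 = 66.7%.

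**How many tests per sign.** Let x of m malignant and y of b benign nodules show the sign.

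- PPV exceeds prevalence when x/(x+y) > m/(m+b), that is, when xb > ym.
- NPV exceeds 1 − prevalence when (b−y)/(m+b−x−y) > b/(m+b), which also reduces to xb > ym.

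So PPV and NPV of one sign in one imaging state are one question. Each sign yields at most two tests, before and after fluorescein.

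**Chance of false confirmation.** Inputs from the Protocol: 20 malignant and 10 benign in discovery; 48 patients in confirmation. Assumptions: the same 2:1 mix in the 48 (48 × 20/30 = 32 malignant, 16 benign); useless signs, each present in 50% of patients; signs and the two readings independent; the same rule at both steps. With d and v the exact binomial probabilities of passing discovery and confirmation, and k signs read twice, the risk is 1 − (1 − d·v)^(2k).

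| Rule at both steps | d (20/10) | v (32/16) | 1 sign | 5 signs | 10 signs |
|---|---|---|---|---|---|
| One-sided Fisher p ≤ 0.05 | 0.0257 | 0.0260 | 0.1% | 0.7% | 1.3% |
| PPV ≥ 0.80 | 0.0796 | 0.0336 | 0.5% | 2.6% | 5.2% |
| PPV ≥ 0.75 | 0.1982 | 0.1304 | 5.1% | 23% | 41% |
| PPV above prevalence | 0.4491 | 0.4596 | 37% | 90% | 99% |

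Example, PPV ≥ 0.75 with 10 signs: d·v = 0.1982 × 0.1304 = 0.0258, and 1 − (1 − 0.0258)^20 = 0.41.

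**Sensitivity to sign frequency (10 signs, two readings).**

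| Rule at both steps | Sign in 30% | Sign in 50% | Sign in 70% |
|---|---|---|---|
| One-sided Fisher p ≤ 0.05 | 0.8% | 1.3% | 1.0% |
| PPV ≥ 0.80 | 37% | 5.2% | 0.1% |
| PPV ≥ 0.75 | 80% | 41% | 7.8% |
| PPV above prevalence | 99% | 99% | 99% |

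The risk under a fixed PPV cut-off moves a great deal with how common the sign is. The risk under a test of association hardly moves.

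**The case against.** The strongest reply is that the Protocol does have a hierarchy. Sections III.2.1 and III.2.2 rank localisation above differentiation, sections III.3.1 and III.3.3 follow that order, and section III.3.2 sizes the trial on localisation. The Experimental plan, Statistical evaluation and section III.3.1 also define validity by the 90% localisation criterion alone. All of that stands. A reader might infer from the summary lists that the trial has no hierarchy, or no defined conclusion when one criterion passes and the other fails. The documents support neither reading. The fault is that the summary lists contradict the ranking.

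The reply continues that signs are described in one group and assessed in another, with a blinded reader for the second. That also stands, and it matters. A reader might treat PPV and NPV in two imaging states as four chances per sign, or take the best of many signs straight into the 48 patients. The first fails because PPV and NPV from one table ask the same question. The second fails because it skips the discovery step: with PPV of at least 0.80 required at both steps and one reading per sign, the risk is only 1.3% for 5 signs and 2.6% for 10.

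Finally, multiplicity control within a secondary objective may sit in a statistical analysis plan that is not shown, so its absence is not held against the Protocol. What the reply does not remove is the contradiction over status, or the undertaking to confirm by predictive values with no reference value. The split protects only under a strict rule, and the Protocol states none.

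**Conclusion.** The point holds in a limited form. The Protocol contradicts itself on whether differentiation is a main or a secondary question. Since alpha, power and sample size cover localisation only, the trial cannot carry a main confirmatory claim on differentiation. Separately, confirmation in the 48 patients has no defined meaning, against an expected PPV of 67% for an uninformative sign.

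For ten useless signs, the risk of false confirmation runs from about 1% to about 99% depending on a rule that is not stated; for a single sign it runs from 0.1% to 37%. These figures rest on the 2:1 case mix carrying over to the 48, 50% sign frequency, independence between signs and readings, and the same rule at both steps. The thresholds and numbers of signs are illustrations and do not come from the Protocol. The figures therefore show how much depends on the missing rule; they do not estimate this trial's actual error rate.

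Severity is minor to moderate: the localisation analysis is unaffected, but the differentiation claim cannot be interpreted as written.

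**What to change.** 1. In both copies of the objectives and main-criteria lists, make localisation the only main criterion and list differentiation as secondary. Replace the verb in objective 2 with one that fits a secondary objective, such as assess.
2. Before any confirmation image is read, lock one sign or combined rule and one imaging state, before or after fluorescein. Call it confirmed only if its PPV exceeds the cancer prevalence observed in the confirmation patients, shown by a single one-sided 5% test of association. That holds the risk of false confirmation at no more than about 5%, however many signs were screened in development.
3. Report all other signs, and the other imaging state, as exploratory with confidence intervals.
4. Reconcile the development set size: 30 in the Experimental plan, Statistical evaluation and III.3.3, against 38 in IV.6.

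The cost is a wording amendment and one documented decision at the end of development, with no extra patients, readers or procedures. The downside is that only one sign or rule can be called confirmed.

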**Experimental plan:**

Multicentric prospective controlled trial, conducted in three academic centers, specialized in interventional bronchoscopy, equipped with both navigational bronchoscopy and probe based confocal microendoscopy techniques.

Subjects with peripheral lung nodule requiring navigational bronchoscopy will be included in the study and explored using both Confocal endoscopy AND navigational bronchoscopy. Confocal probe will be inserted in the same catheter as used for the navigational bronchoscopy and confocal images will be recorded before and after fluorescein IV injection, and before sampling.

In this study, positive diagnostic criteria for the localization of peripheral nodule using confocal imaging is a solid pattern as opposed to the usual loose fibered network pattern of the normal alveolar duct. According to this criteria, the confocal imaging procedure will be considered as valid if the number of lesions localized by confocal is not inferior to 90 % of those localized by navigational bronchoscopy. Therefore, pCLE will prove valid if it can recognize at least 70 subjects out of the 78 / 120 subjects for which the navigational bronchoscopy is forecasted to localize the peripheral lesion (Cohen concordance Kappa value of 0,74 between confocal and navigational bronchoscopy).

A secondary objective will be to describe specific signs of cancer using confocal endoscopy . This will be assessed on the first 30 patients using confocal imaging obtained before and after fluorophore IV injection, in comparison to histology, and confirmed on the following 48 patients.

## **2.6 Clinical research project, English version**

This part will include:

- Problem, hypothesis and objective of the investigations ·
- Location of the work in the context of the current knowledge ·
- detailed description of the methodology (number of necessary subjects:)
- detailed description of the implemented techniques ·
- Plan of realization of the describing project:
  - the role of every team
  - a projected calendar adapted to the duration of the project -
  - the identification of the key stages,
  - the modalities of coordination of the project
  - the capacity of patients' inclusion

**Synopsis :**

The aim of this trial is to assess probe based confocal microendoscopy of the lung (Alveoscopy) for in-vivo diagnosis of peripheral lung nodules and masses, in comparison to modern endoscopic techniques of peripheral lung nodule localisation and sampling (endobronchial ultrasound : EBUS, and electromagnetic navigation : EMN).

**Objective(s) of the clinical study**

1. To demonstrate that confocal endomicroscopy is not inferior to navigational endoscopy for the localisation of peripheral lung nodule
2. To demonstrate that confocal endoscopy can differentiate benign from malignant tumors

**Main assessment criteria:**

1. number of lesions localized by confocal endoscopy compared to navigational bronchoscopy
2. Positive and negative predictive values of confocal signs before and after IV fluorophore injection for the diagnosis of cancer.

**Experimental plan:**

Multicentric prospective controlled trial, conducted in three academic centers, specialized in interventional bronchoscopy, equipped with both navigational bronchoscopy and probe based confocal microendoscopy techniques.

120 subjects with peripheral lung nodule requiring navigational bronchoscopy will be included in the study and explored using both Confocal endoscopy AND navigational bronchoscopy. Confocal probe will be inserted in the same catheter as used for the navigational bronchoscopy and confocal images will be recorded before and after fluorescein IV injection, and before sampling.

**Statistical evaluation :**

In this study, positive diagnostic criteria for the localization of peripheral nodule using confocal imaging is a solid pattern as opposed to the usual loose fibered network pattern of the normal alveolar duct. According to this criteria, the confocal imaging procedure will be considered as valid if the number of lesions recognized by confocal is not inferior to 90 % of those localized by navigational bronchoscopy. Therefore, pCLE will prove valid if it can recognize at least 71 of 78 nodules / subjects efficiently sampled using navigational bronchoscopy (Cohen concordance Kappa value of 0,74 between confocal and navigational bronchoscopy).

A secondary objective will be to describe specific signs of cancer using confocal endoscopy . This will be assessed on the first 30 patients (including 20 cancers) using confocal imaging obtained before and after fluorophore IV injection, in comparison to histology, and confirmed on the following 48 patients.

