#### **III.3. Patient number, statistical analysis**

##### *III.3.1. Principal criteria analysis :*

In this study, we will consider that, to be valid for the diagnosis of peripheral nodule, alveoscopy should recognize 90% or more nodules that are successfully localized and sampled using navigational bronchoscopy techniques.

Positivity criteria for alveoscopy is defined as in-vivo imaging of a solid pattern and a conclusive biopsy sampling (benign or malignant) of the lesion during one of the navigational attempt to localize the lesion. Alveoscopy will be considered negative if a normal pattern is observed, with a conclusive biopsy of the nodule in the same location.

Navigational bronchoscopy results will be considered positive in case of conclusive biopsy at the first attempt of localisation of the lesion during bronchoscopy.

Therefore, there is a possibility that final results of the study show superiority of confocal imaging over navigational bronchoscopy , if pCLE allows for a better control and correction of the position of the navigational probe during the procedure.

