### *III.3.2. Number of subjects.*

Because each patient is evaluated by both navigational bronchoscopy and confocal procedure, the required number of patient can be calculated based on a non-inferiority test for paired data. (Tango T. Equivalence test and confidence interval for the difference in proportions for the paired-sample design, Statistics in medicine 17, 891-908, 1998.) . According to this test, 78 patients positive for navigational bronchoscopy are needed to show a 10 % performance difference between the techniques (alpha risk 5%, Power 80%). This proportion corresponds to a 0,74 concordance using Cohen Kappa test. Forecasted sensitivity of navigational bronchoscopy being 65%, the total number of patients required for the study is 120.

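### The primary success rule is given as two conflicting raw counts (at least 70 and at least 71 of 78), and neither count controls the stated 5% alpha

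*Protocol*

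**What the plan says.** The success rule appears in three places.

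- Protocol, opening summary, Experimental plan: "pCLE will prove valid if it can recognize at least 70 subjects out of the 78 / 120 subjects" in whom navigation is forecast to find the lesion.
- Protocol, Synopsis, Statistical evaluation: the method is "valid if the number of lesions recognized by confocal is not inferior to 90 % of those localized by navigational bronchoscopy", from which the text concludes that "pCLE will prove valid if it can recognize at least 71 of 78 nodules / subjects".
- Protocol, III.3.1: "alveoscopy should recognize 90% or more nodules that are successfully localized and sampled using navigational bronchoscopy techniques".

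The first two places both attach a kappa of 0.74 to their count. None of the three mentions a test or a confidence limit.

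Section III.3.2 gives the inferential frame: "the required number of patient can be calculated based on a non-inferiority test for paired data", citing Tango's method, with a 10% difference and "alpha risk 5%, Power 80"%. It uses the method only to derive the 78 navigation-positive patients, and hence 120 in total at a forecast sensitivity of 65%. It does not say whether the 5% is one-sided or two-sided.

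**The concern.** There are two faults in the rule that decides the primary conclusion.

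First, the counts differ. A result of 70 of 78 is a success in the opening summary and a failure in the synopsis and under III.3.1.

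Second, the stated objective is to demonstrate non-inferiority, and an alpha is named, but the rule that declares validity is an observed count sitting at the limit. An estimate at the limit does not show that the true value lies on the right side of it. The trial could therefore report a demonstrated non-inferiority that the test used to size it would not support.

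**Working it through.** **Inputs.** 78 navigation-positive patients, 120 in total, 65% sensitivity, 10% margin, alpha 5%, power 80%, kappa 0.74 (III.3.2); pass marks 70 and 71 (opening summary and synopsis); 90% criterion (all three places).

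**1. The plan's own sample size.** 78 / 0.65 = 120, as stated. For 78, the discordant proportion is not given. If both techniques are positive in 65%, kappa 0.74 implies (1 - 0.74) x 2 x 0.65 x 0.35 = 0.1183. The paired formula at one-sided 5% then gives 0.1183 x (1.645 + 0.842)² / 0.10² = 73.1, so 74. Exact power of Tango's test with 78 pairs is 78.1%. The figure of 78 is therefore roughly reproduced, under an assumed discordance.

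**2. The two counts against the 90% criterion.** 0.90 x 78 = 70.2. 70/78 = 89.7% fails; 71/78 = 91.0% passes.

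**3. The two counts against kappa.** Take 78 of 120 positive on each technique, so chance agreement is 0.65² + 0.35² = 0.545.

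- 71 recognised, 7 v 7 discordant: agreement (71 + 35)/120 = 0.883; kappa = (0.883 - 0.545)/0.455 = 0.744.
- 70 recognised, 8 v 8 discordant: agreement (70 + 34)/120 = 0.867; kappa = 0.707.

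Only 71 matches 0.74.

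**4. Error rate if the margin is 90% recognition among navigation-positive nodules** (as the synopsis and III.3.1 word it). With X ~ Binomial(78, 0.90):

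| Pass mark | P(pass) at true 90% | One-sided 95% exact lower limit at the mark |
|---|---|---|
| 70 | 62.2% | 82.3% |
| 71 | 47.5% | 83.8% |

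The smallest count with P(X >= k) at or below 5% is 75 (actual alpha 4.1%, lower limit 90.4%).

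**5. Error rate if the margin is 10 points over all 120 patients.** A 10-point loss is 12 patients, so confocal imaging finds 66. With no confocal-positive/navigation-negative patients, recognition among navigation-positives is 66/78 = 84.6%, and P(pass) is about 13% (70) or 7% (71). If some such patients exist, recognition at the same net loss is lower and so is P(pass): at 82% it is about 4% or 2%.

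**6. Does the count agree with Tango's test over 120 pairs?** The limit is -10 points, the critical value at one-sided 5% is z = 1.645, and all 120 are taken as classified on both techniques.

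| Recognised of 78 | Confocal-positive/navigation-negative | z |
|---|---|---|
| 71 | 0 | 1.52 (p = 0.064) |
| 71 | 1 | 1.73 (p = 0.042) |
| 71 | 7 | 2.75 (p = 0.003) |
| 70 | 0 | 1.22 |
| 70 | 2 | 1.63 |
| 70 | 3 | 1.82 |
| 70 | 8 | 2.65 |

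The same count can pass or fail the test. 71 with no compensating patients meets both written marks but fails the test; 70 with 8 such patients misses the 71 mark but passes the test clearly.

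**The case against.** The strongest reply is that the 5% belongs to the paired test in III.3.2, not to the count, and that the paired comparison is what the protocol intends. The main criterion compares the numbers of lesions localised by each technique. III.3.1 scores navigation on its first attempt but confocal imaging on any attempt, and allows that confocal imaging may prove superior, which is impossible unless some patients are confocal-positive and navigation-negative. The kappa of 0.74 also fits a table of 120 pairs; 7 misses with no compensating patients would give 0.877. Much of this stands. A reader might infer that the false-positive rate simply is 48-62% instead of 5%. The documents support that only on the reading in step 4.

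A reader might also infer that 75 of 78 is the correct pass mark. That too follows only from step 4, and it is costly: power is 45% at true recognition of 95% and 79% at 97%, against the planned 80%.

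It can further be said that applying Tango's test in the final analysis may be left to a statistical analysis plan not shown, and that the number of navigation-positives will naturally vary around 78. Both are fair. The variation is not an error, since the criterion of 90% or more in III.3.1 works for any denominator. But the protocol itself fixes what makes the method valid, in two incompatible versions. An analysis plan that let the test decide would contradict that text, so the text still needs correcting.

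**Conclusion.** The point holds in this form. The two counts contradict each other, 70 fails the protocol's own criterion, and 71 is the one consistent with both the 90% and the kappa. This part rests on no assumption beyond the kappa table having 78 positives on each technique.

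Neither count controls alpha at 5%. The excess is large (62% or 48%) if the margin is conditional on navigation-positives. It is modest (at most about 13% or 7%) if the margin is 10 points over all 120, where the main defect is instead that the count ignores patients who enter the test. Both sets of figures assume exactly 78 navigation-positives. The documents do not settle which margin is meant, so neither set should be quoted without its condition. The unstated sidedness of the 5% does not change the conclusion: at one-sided 2.5% (z = 1.96), 71 of 78 with up to 2 confocal-positive/navigation-negative patients (z = 1.92) would also fail.

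**What to change.** In the opening summary's Experimental plan, the synopsis's Statistical evaluation and III.3.1, replace the count with one rule that works for any number of navigation-positives: non-inferiority is declared if the lower confidence limit of Tango's paired interval for confocal minus navigation, over all patients, is above -10 points, at one-sided 5% or another stated level. Report recognition among navigation-positives with its confidence interval. Keep 71 of 78 (not 70) only as a descriptive target.

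If the sponsor wants the claim among navigation-positives only, require the lower limit for recognition to exceed 90% (75 of 78 when n is 78) and replace the 80% power by the true figures (about 45% at 95% recognition, 79% at 97%).

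The cost is wording in three places, a restated power and, on the second option, a much stricter pass mark. No extra patients are required by the change itself. On the first option the formula in step 1, with the same discordance and equal performance, gives power Φ(0.10 x √(120/0.1183) - 1.645) = Φ(1.54), about 94%, for 120 pairs. This is approximate: with 78 pairs the formula gives 82% against an exact 78%.
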